## Abstract

**Background:**

High-quality contraceptive counselling can accelerate global efforts to reduce the unmet need for and suboptimal use of modern contraceptives. This study aims to identify a package of interventions designed to strengthen in Pakistan and Nigeria and determine their effectiveness in increasing client-level decision-making, autonomy and meeting of contraceptive needs.

**Methods:**

A multisite, two-stage and five-phase intervention design will start with a pre-formative, formative, design, experimental and reflective phase. The pre-formative phase will map potential study sites and establish the sampling frame. The two-part formative phase will first use participatory approaches to identify clients’ perspectives, including young couples and providers, to ensure research contextualisation and address each interest group’s needs and priorities followed by clinical observations of client–provider encounters to document routine care. The design workshop in the third phase will result in the development of a package of contraceptive counselling interventions. In the fourth experimental phase, a multi-intervention, three-arm, single-blinded, parallel cluster randomised-controlled trial will compare routine care (arm 1) with the contraceptive counselling package (arm 2) and the same package combined with wider methods availability (arm 3). The study aims to enrol a total of 7920 participants. The reflective phase aims to identify implementation barriers and enablers. The outcomes are clients’ level of decision-making autonomy and use of modern contraceptives.

**Ethics and dissemination:**

Ethical approval for this study was obtained from the WHO Scientific and Ethics Review Committee (Protocol ID Pakistan: ERC 006232 and Nigeria ERC: 006523). Each study site is required and has obtained the necessary ethical and regulatory approvals that are required in each specific country. Findings will be presented at local, national and international conferences and disseminated by peer-review publications.

**Trial registration number:**

NCT06081842.

STRENGTHS AND LIMITATIONS OF THIS STUDYA mixed-method study design offers valuable insights and can address research questions that quantitative or qualitative methods alone cannot adequately answer.Multicentre research offers several benefits compared with studies done at a single centre such as access to a larger diverse sample, the ability to pool resources and foster connections and collaborations among researchers.The study will be implemented in a limited geography of the target countries; therefore, caution needs to be taken before generalising the findings.

## Background

Overlooking women’s and couples’ need for quality contraceptive counselling constitutes a missed opportunity in family planning programmes and services to ensure equitable access to the health, social and economic benefits of modern contraception for women, men and adolescents. Access to family planning is a human right enshrined in the United Nations’ Sustainable Development Goal 3 on health and well-being and, specifically, its target 3.7: *ensure universal access to sexual and reproductive health-care services, including for family planning*.^1^ Around 164 million women of reproductive age have an unmet need for modern contraceptive methods despite increased contraceptive use over the past decades.^2^ Satisfying the unmet need for contraception in low-income and middle-income countries and offering all pregnant women and their newborns the standard care recommended by the WHO would result in dramatic reductions of unintended pregnancies by 68%, unsafe abortions by 72%, maternal deaths by 62% and neonatal deaths by 69%.^3^ Adequate contraceptive coverage among users can be improved by addressing suboptimal use and high discontinuation rates.^4^

Effective contraceptive counselling can help individuals choose a method that meets their needs and preferences, manage any side-effects and continue using their preferred method or switch to an alternative one.^5^ Contraceptive counselling could improve the effective use of modern contraception and reduce unmet need according to a systematic review that synthesised the evidence on the comparative effectiveness of different contraceptive counselling strategies.^6^ The quality of contraceptive counselling in low-resource settings is often low. In Senegal, for example, only 18% of providers counselled their clients on the three-item Method Information Index (method use, side-effects and timing of follow-up visits).^7^ Interventions targeting women requesting or initiating a chosen method, including structured counselling on side-effects, tend to show positive effects on contraceptive continuation.^8–11^ Counselling interventions targeting family planning service users,^12–16^ abortion service users,^17–19^ postpartum women^20–25^ and those reached by community-based interventions^26–28^ have inconsistent effects on contraceptive behaviour and satisfaction outcomes. In contrast, increased contraceptive use often follows interventions introducing systematic contraceptive counselling among women attending non-family planning outpatient services.^29–31^ However, these interventions often include expanded contraceptive method provision, and the observed changes cannot be attributed to counselling alone. High-quality evidence is generally limited, and no clear consensus exists on how best to deliver contraceptive counselling to meet clients’ contraceptive needs and enhance their satisfaction.

Building on this systematic review, the WHO organised a geographically diverse think tank in May 2019 in Geneva, Switzerland, to identify research and guidance gaps and other opportunities to improve the quality of contraceptive counselling.^32^ Equally important was the crafting of a definition on contraceptive counselling, which was adopted by think tank members^33^ : *Contraceptive counselling is defined as the exchange of information on contraceptive methods based on an assessment of the client’s needs, preferences and lifestyle to support decision-making as per the client’s intentions. This includes the selection, discontinuation or switching of a contraceptive method. The key principles are based on coercion-free and informed choice; neutral, understandable and evidence-based information; collaborative and confidential decision-making process; ensuring respectful care, dignity and choice*. The definition took into consideration the core dimensions articulated in the literature and mirrors the principles that were deliberated by the think tank: a two-way discussion and decision-making process between the client and provider, sharing objective and user-friendly information, and fundamentally grounded in the rights to autonomy, dignity, privacy, respect and participation, among others. In addition, person-centeredness is a critical component of quality in family planning.^5^ The four-item person-centred contraceptive counselling scale (PCCC) is a valid and reliable measure of person-centred contraceptive counselling that reflects patients’ perspectives on contraceptive counselling.^34^ For example, integrating Dehlendorf’s four-item validated tool: PCCC: person-centred contraceptive counselling scale: Think about your visit. How do you think the member of the healthcare team did? Please rate them on each of the following by circling a number (the scale will use—Poor, Fair, Good, Very good and Excellent). Hence, to measure decision-making autonomy, the following considerations need to factor:

Respecting me as a person.Letting me say what mattered to me about my birth control method.Taking my preferences about birth control seriously.Giving me enough information to make the best decision about my birth control method.

Furthermore, the think tank members agreed on a prioritised set of guidance, knowledge and implementation research gaps.^32^ Such gaps include, for example, understanding or identifying clients’ experiences with and expectations of counselling in a variety of global settings; the types of settings different populations, particularly adolescents, unmarried women, migrants, gender non-conforming people and religious/ethnic minorities, receive most of their contraceptive counselling and the quality of counselling across these settings; the fluidity/ambivalence of pregnancy intentions, risk perception (pregnancy and sexually transmitted infections) and women’s understanding of their bodies; the independent effect of counselling from method provision; the core elements of high-quality of contraceptive counselling and how these differ by context and what provider characteristics affect counselling quality; the minimum skills and competencies for contraceptive counsellors; the contents of a comprehensive package of best practices for Family Planning (FP) counselling for different populations.

We have reviewed and used the currently available resources noted above such as person-centred care and effective contraceptive counselling approaches, which focus on persons’ values and preferences, and are considered to improve the quality of care in family planning. These approaches are likely to promote greater patient autonomy, trust and satisfaction with services. Majority of the research has been based on small, qualitative studies. This study, using a mixed-methods approach, will benefit from existing resources and will also highlight the rights-based approach in the counselling package to understand and document its implementation and effectiveness in the context of two countries.

### Study overall objective and hypothesis

Owing to these gaps combined with the sociocultural challenges related to accessing contraception, we propose a multisite, two-stage and five-phase study with two main objectives. The objective is to identify and test the effectiveness of a contraceptive counselling intervention bundle on improving clients’ informed decision-making autonomy as well as meeting their need for family planning. The outcomes are changes in clients’ decision-making autonomy and clients’ met need for family planning. The secondary outcome will be a change in modern contraceptive prevalence.

The research rests on the working hypotheses that the package will strengthen existing contraceptive counselling services; incorporate perspectives of key stakeholders such as clients and providers; align with national health policies and WHO global standards and address challenges related to limited public resources.

### Study countries: Pakistan and Nigeria

#### Pakistan

The study will be implemented in Pakistan in partnership with the Ministry of National Health Services, Regulations and Coordination. The overall demographic, family planning and reproductive health indicators based on the 2017–2018 Demographic and Health Survey^35^ note that rural settings fared worse than urban settings. The total fertility rate was 3.6 children per woman, modern contraceptive prevalance rate was 25%, overall unmet need for family planning was 17% and the demand for family planning satisfied by a modern method was 49%. In terms of family planning knowledge, more than 98% of urban and rural women had heard about any type of modern methods—before marriage, only 15% of women did. Regarding men’s attitudes toward contraceptive use, 27% believed that family planning use is a woman’s business, while 16% thought it may encourage women to be promiscuous.^36^

#### Nigeria

The study will also be implemented in Nigeria by College of Medicine, University of Ibadan. The study will be conducted in two study sites: Lagos (southern part of Nigeria) and Kano (northern part of Nigeria) states. These states were selected for the following reasons: (1) data from the Performance Monitoring for Action programme are available for both states from annual surveys over the past 3 years, including information on the method information index plus and other family planning indicators (pmadata.org); (2) the team has a good network in both locations and will be able to readily collaborate with the State Ministries of Health and (3) safety and security are relatively good with no serious threats in recent times.

The latest demographic, family planning and reproductive health indicators based on the 2018 Demographic and Health Survey in Nigeria in 2019 showed that in general, rural settings fared worse than urban settings.^37^ The total fertility rate was 5.3 children per woman; overall unmet need for family planning was 18.9%; demand for family planning satisfied by a modern method was 33.9% and modern contraceptive prevalance rate was 12%. In terms of family planning knowledge, 93.9% of currently married women and 98.3% of sexually active unmarried women had heard about any type of modern contraceptive method.

## Methods

### Framework and perspectives

#### Theory of change

This health services research is guided by the theory of change framework and incorporates perspectives on human rights and the health system to develop a contraceptive counselling intervention package that strengthens existing family planning services and ensures effectiveness, safety and cultural appropriateness. Following the research findings, the long-term vision is to support the health system in developing a sustainable and scalable contraceptive counselling intervention package for Nigeria and Pakistan. Although the exact package has not yet been developed, based on the requirement set by the respective ministry of health/population in Pakistan and Nigeria, the researchers are willing to contribute to the development of provider training, post-training mentorship and the provision of Information, Education and Communication (IEC) materials to enable the implementation of the intervention bundle.

The theory of change underpins the staged and phased strategy used in this trial, which includes key objectives, activities and intermediate and final results (refer to figure 1).^38^

**Figure 1 F1:**
[figure not shown]
Overall study model.

##### Health system perspective

First and related to the research model outlined in figure 1, the study will rely on the WHO Health System Framework with its six system building blocks and link research and programmatic considerations for contraceptive counselling.^39^ The six foundational components of health systems are leadership/governance, healthcare financing, health workforce, medical products and technologies, information and research, and service delivery.^39^

##### Human rights perspective

The research will use the WHO Framework for Ensuring Human Rights in the Provision of Contraceptive Information and Services.^40^ The human rights framework comprises nine standards that interweave with the dimensions of quality of care: quality, acceptability, availability, accessibility, non-discrimination, participation, accountability, informed-decision making, and privacy and confidentiality. The research team would ensure a person-oriented approach where no teenage girls or women are discriminated against (eg, in receiving family planning information and services) because of their marital status, age, HIV status, minority status or other social or medical factors.^33^

With regard to the participation standard, the research will ensure active and informed participation of individuals in decision-making that affects them, including on matters related to their health.^41^ Due to the complex social, cultural and religious challenges and opportunities surrounding contraceptive use, our research design will assume that the following participatory action research (or participatory research) principles will be essential to meet the study objectives as well as gain insights into the implementation process.^42^

#### Study phases and timelines

The research entails a complex multisite, two-stage and five-phase (figure 1): Stage 1 is formative and will comprise a pre-formative (phase 1) and a formative (phase 2), while Stage 2 is experimental and will include intervention design (phase 3), experimental (phase 4) and reflective (phase 5). The methods proposed for each phase are not inherently complex; however, the intervention in its globality is complex due to the number and difficulty of behaviours required by both the intervention deliverers and recipients, and the involvement of multiple organisational levels or groups targeted by the intervention, among other factors.^43^ The design adheres to recommendations from the for developing a complex intervention, assessing its feasibility and facilitating its implementation and evaluation.^43^ As such, the phases are interlinked and have key objectives, methodologies and outcomes.

##### Stage 1

The pre-formative phase aims to establish a sampling frame of potential study sites by mapping primary health centres based on set criteria. Eligibility criteria for health centres include: (1) provision of family planning services; (2) availability of at least three to four modern contraceptive methods, including a barrier method (eg, condom) and short-term and long-term methods (eg, pills, injectables, implants, intra-uterine devices); (3) absence of contraceptive stock-outs over the preceding 3 months in alignment with national policy; (4) a minimum average of 25 family planning encounters per week (or 100 per month) at selected high-performing facilities (both public and private) and at least 12 encounters per week (or 48 per month) at selected low-performing facilities (again, both public and private); (5) non-receipt of family planning technical support (eg, capacity building, supplies) from other organisations at recruitment, with a commitment to refrain from such support during the study and (6) willingness to participate in the study. Based on this sampling frame, four health centres (public and private sector) will be allocated to the formative phase while the others will be randomised to each arm of the experimental phase. The specific objectives of the *formative phase* are to (1) document the in-clinic contraceptive counselling routine using observation checklists and (2) seek through qualitative research the perspectives of clients, including young people, providers and other stakeholders to ensure adequate contextualisation of the research and address needs and priorities of each interest group regarding contraceptive counselling barriers and enablers.

##### Stage 2

The specific objective of the *intervention design phase* is to co-design, based on the results of the formative phase and through a participatory and consensus-building approach engaging clients, providers and other main actors, a package of contraceptive counselling to be implemented during the experimental phase. To be integrated into the final package, interventions will need to consider current human resources and clinical capacity, costs, acceptability, feasibility, scalability and other field considerations.

The objective of the *experimental phase* is to assess, using a cluster randomised controlled trial (RCT) design, the impact of the contraceptive counselling bundle on clients’ level of decision-making autonomy and demand satisfied for family planning. The three-armed cluster RCT comprises (1) a control arm with contraceptive counselling and care and a range of family planning methods that are available at field level per the national policy and guidelines; (2) an experimental arm implementing the contraceptive counselling package but still with a range of family planning methods that are available (upto four methods) per the national policy and guidelines at field level and (3) another experimental arm with the contraceptive counselling package but with an expanded range of family planning methods (more than four methods) that are recommended by national policy and guidance.

The *reflective phase* objective is to determine operational barriers and catalysts related to the package implementation using qualitative research. Once the package of interventions has been identified—and resources permitting, we might consider conducting a cost-effectiveness analysis to determine the counselling package cost-effectiveness.

The qualitative research and cluster RCT are detailed in the following sections.

### Timelines

The study be tenataively initiated in November 2023 and it will be completed by November 2025. The analysis and report will be drafted by June 2026.

### Qualitative research

#### General design

For the qualitative research components of the study during the formative and reflective phases, we will conduct in-depth interviews (IDIs) in Pakistan and Nigeria with various community members (including women, adolescent males and females, partners and influential individuals), health personnel (such as clinicians, managers and community health workers—CHWs), development partners, donor agencies and national policymakers. The formative phase will involve selecting four health centres (both public and private) and their respective coverage areas in each country using a convenient sampling approach. These sites will be chosen from the sampling frame established during the pre-formative phase.

To identify barriers and facilitators related to contraceptive counselling, separate IDIs will be conducted with groups of 6–10 participants from the following categories: (1) women who have used family planning services at the health centre within the past 12 months: married and unmarried adolescent females (≤19 years), married and unmarried women 19–39 years, married and unmarried women ≥40 years (The study will include Women of Reproductive Age (WRA)—irrespective of their marital status and age group (including migrants refugee people, ethnic and religious minorities, women or men with disabilities, women or men with HIV, etc are inclusive)); (2) married and unmarried men who are husbands or partners of clients who have used family planning services at the clinic within the past 12 months, and married and unmarried adolescent males (<19 years) and (3) family planning service providers.

About the recruitment of men/male participants, the women participants will be first recruited based on their eligibility and recruitment criteria. If the female participant is selected, she will be asked whether she is using the FP method in consensus with her male partner/spouse or using it covertly. If she uses the FP method with the consensus of her male partner/spouse, we will recruit the accompanying male partners/spouses in the study. If the women participant is using the FP method covertly, then the women will be first asked to provide consent to be invited to study participation. If she does not consent, then men/male participants will be identified by the CHWs at the community level. In both cases, formal consent will be taken from the woman whether she is using the FP method covertly or in consensus with her male partner/spouse.

IDIs will also take place with clinic managers, supervisors, CHWs, policymakers and other influential individuals/opinion leaders (selected purposively) who have observed, supervised or monitored family planning services at/or the catchment of the selected public/private health facility. We anticipate that interviews will last between 45 and 60 mins and will take place in a safe, neutral space of the participant’s choosing (eg, town hall, office space, on porch outside participant’s home, etc). Both the recruiter and the participant will decide and agree on the location of the interview and this will be conveyed to the research team. Alternatively, the team will also identify pay-per-hour spaces as an option to present to the participant. The interview guides will address several key themes pertinent to contraceptive counselling, including: practices, attitudes and knowledge regarding contraception; health systems and sociocultural challenges and enablers affecting contraceptive use; and quality of care, encompassing autonomy, informed decision-making and other human rights considerations in contraceptive services.

These themes will guide the exploration of participants’ perspectives and experiences related to contraceptive counselling within the broader context of reproductive health services.

The qualitative research in the *reflective phase* will occur in three health centres in each of the three study arms (nine centres in total). The centres will be purposely sampled to include the lowest, average and highest performing ones in terms of measured outcomes to enable the broadest possible understanding. Aligned with the theory of change framework, the qualitative research will conduct an implementation evaluation to examine challenges and facilitators associated with the provision of contraceptive counselling and family planning services, assess fidelity to the intervention within experimental groups and explore strategies for potential scalability. IDIs will be conducted separately with service providers, clients across different age groups (≤19 years, 20–39 years, ≥40 years) and clinic managers. The interview guides will address the following topics related to contraceptive counselling: quality of care including autonomy in decision-making and other human rights perspectives, operational challenges and facilitators, and considerations for scaling up the intervention

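### As written, the community route for recruiting men lets an adult man be approached as a clinic client's partner without that woman's agreement, which may disclose covert contraceptive use

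*Protocol article*

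**What the plan says.** All the rules at issue stand in the protocol article under Qualitative research, General design.

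- **Who is eligible.** The male category covers "married and unmarried men who are husbands or partners of clients who have used family planning services at the clinic" in the past 12 months, "and married and unmarried adolescent males (<19 years"). The partner condition is attached to the first group. The adolescent group is listed after it without one.
- **Order of recruitment.** Men are reached through women: "the women participants will be first recruited based on their eligibility and recruitment criteria", and each selected woman is asked whether her use is agreed with her partner or covert.
- **Agreed use.** Here "we will recruit the accompanying male partners/spouses in the study".
- **Covert use.** Where a woman reports this, the text provides that "the women will be first asked to provide consent to be invited to study participation". The fallback follows: "If she does not consent, then men/male participants will be identified by the CHWs at the community level".
- **Closing sentence.** "In both cases, formal consent will be taken from the woman whether she is using the FP method covertly or in consensus" (that is, by agreement between the couple).

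Elsewhere, Selection criteria and recruitment approach names community health workers (CHWs) from the providers' catchment area among the recruiters and has them trained in ethics and consent. Qualitative data management and analysis promises private interviews. The Human rights perspective section lists privacy and confidentiality among the standards the research will use.

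**The concern.** The section handles covert users separately, so the hazard was recognised. But the fallback applies when such a woman has not consented, and it hands the search for men to people who work in the same catchment area. If those men must still qualify as partners of clinic clients, the ground for approaching a man is itself a fact about a woman's use of the clinic. If she has not told him, the invitation could be how he finds out.

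What is at stake is the safety and confidentiality of women, some of whom may not be study participants at all. The article gives some reason to take this seriously: for Pakistan it reports that 16% of men thought family planning may encourage women to be promiscuous. Nothing in the trial's error rates, power or outcome analysis depends on the point.

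**Working it through.** No arithmetic applies, and the plan states no figure to reproduce. The check is to follow the rules in order and see what each permits.

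**1. Does the partner condition carry over to the community route?** The eligibility list sets it for adult men. The fallback sentence neither repeats nor waives it. Without a waiver, the eligibility rule continues to apply to adult men. It does not apply to adolescent males on the plain reading of the list.

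**2. Which men may a CHW identify?** Two readings are open.

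| Reading | What the text permits | Who could be exposed |
|---|---|---|
| The refusing woman's own partner may be found this way | Nothing excludes him | The woman who refused |
| Substitute men are sought (the more natural reading) | Each adult man must still be some client's partner | A different client |

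**3. Has the exposed woman been asked?** On the first reading she was asked and did not consent. On the second, the question about covert use is described only for women who were themselves recruited. Nothing says that the substitute man's partner is asked before he is approached.

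**4. Does the consent wording close the gap?** The covert-use step does not say who is to be invited, the woman or her partner. The closing sentence explains its two cases as covert and agreed use, so it most plausibly says that the woman's consent is taken under either kind of use. It does not say whether that consent is to her own participation, to contact with her partner, or to both. It also does not mention the partner of a substitute man.

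**5. Do the general safeguards reach this contact?** Training in ethics and consent is general, with no stated rule for covert users. Private interviews protect the conversation, but the disclosure would come earlier, at the invitation.

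**6. How far does it extend?** The male category appears in the formative list, for four centres per country (4 × 2 = 8 centres). The reflective-phase interviews are listed with providers, clients and clinic managers only. The number of covert users is not stated, so no count or rate of exposed women can be derived.

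**The case against.** The strongest reply is that the fallback is itself a safeguard: when a covert user does not consent, recruitment turns away from her and towards other men. That is the natural reading. A reader might infer that her refusal is overridden and her husband approached anyway, but the text does not say so. What stands against the reply is that the text does not rule it out either, and that moving to other men shifts the possible exposure to another client.

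Second, the partner condition is not repeated in the fallback and never covered adolescent males. A reader might conclude that every man found by a CHW must be a client's partner; the document supports that for adult men at most.

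Third, disclosure depends on the invitation script, which is not shown. A CHW may know why a man is eligible without telling him, and a man whose partner uses a method by agreement already knows. The full protocol may hold further rules, and ethics approvals are reported. This is why the risk is called possible. It does not remove the point, because the article sets out the procedure step by step and the steps as given leave the gap.

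Fourth, a reader might see a flat contradiction between taking the woman's consent in both cases and a route that starts from her not consenting. Since the two cases are most plausibly the two kinds of use, the contradiction is not established. Deleting the sentence would also remove the one explicit statement that her consent is taken under covert and agreed use alike. It needs clarifying.

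**Conclusion.** The point holds in a limited form. Taken together, the eligibility rule and the covert-use fallback allow an adult man to be approached as a client's partner without that woman's agreement. This may disclose covert use, and it conflicts with the study's own privacy and confidentiality standard.

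The conclusion assumes that the partner condition still applies on the community route, since nothing waives it, and that no unseen script or procedure already prevents the disclosure. The exposure is limited to adult men approached as clients' partners, in practice those whose partners have not told them, and mainly to the formative phase. Its frequency cannot be estimated from the document. The trial's outcomes, sample size and analysis are untouched. It is a cheap improvement that bears on participant safety.

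**What to change.** Reconcile the eligibility list and the male-recruitment paragraph in General design by stating that:

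- (a) the partner of a woman who reports covert use and does not consent is not approached by any route;
- (b) a man is approached as a client's partner only after that woman has agreed to the contact;
- (c) men found by CHWs are otherwise invited as men living in the catchment area, without the partner-of-client condition and without reference to any woman's use of the clinic;
- (d) the closing consent sentence is kept and clarified to say what the woman consents to: her own participation, contact with her partner, or both.

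A blanket bar on inviting any covert user's partner, even where she agrees, is not needed; item (b) leaves that choice with her.

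The cost is revised wording in the recruitment procedure, matching content in recruiter training, and an ethics notification. The downside is that some of the men interviewed may not be partners of clinic clients, so their accounts may be less directly tied to the service.
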